### Changes to design during the trial

Two changes to the protocol were made during the course of the study.As recruitment was lower than planned, particularly for Māori and Pacific clinicians and participants, it became clear that we would not have sufficient numbers to allow for useful statistical analysis by ethnicity. As a consequence we have reduced the number of planned analyses by ethnicity and adjusted our sample size accordingly. More details are provided in the ‘Sample size’ section. However, we plan to augment the data we will have on the use of MATCH-ADTC for these two populations with a qualitative study of the acceptability of MATCH-ADTC to Māori and Pacific clinicians, participants, and their families.At the request of the Health Research Council’s independent data monitoring committee, who are overseeing the conduct and safety of the trial, we added to the data collection on serious adverse events by collecting information from parents at the three month follow-up interview on ‘moderate’ adverse events. More details on this are given below.

### Ethics approval

Approval has been received from New Zealand’s Health and Disability Ethics Committee (13/CEN/97).

### Setting

This study is being conducted in ten outpatient CAMHS clinics from four provinces in New Zealand (Northland, Auckland, Waikato, and Wellington).

### Participants

Participants are youths and their parents (or guardians), referred to CAMHS for assessment and treatment. Intake clinicians identify potential participants during their standard initial assessment. One self-nominated parent completes the parent-rated assessments.

### Inclusion criteria

Participants are eligible if:They are newly referred to, and accepted for treatment in, CAMHS with a primary disorder that includes anxiety, depression, trauma-related symptoms, or disruptive behavior;They are 7 to 14 years of age on the date of consent;They provide written consent (or verbal assent) and have written parental consent; and,They and their parents speak English.

### Exclusion criteria

Participants are ineligible if:They are currently receiving other psychosocial treatment for their disorder within or outside CAMHS;They have a primary disorder of psychosis, intellectual disability, attention deficit-hyperactivity disorder (where the primary reason for referral is inattention or over-activity), autism, or an eating disorder;They are acutely suicidal; or,They have a sibling who has previously been recruited into the study.

### Withdrawal criteria

Participants (youth and their parents, or study clinicians) can withdraw from the study at any time. Those participants who remain in the study but have dropped out of treatment are followed up wherever possible. Where a clinician withdraws from the study, a clinician from the same treatment arm will continue to provide the treatment allocated (i.e., either MATCH-ADTC or usual care).

### Intervention

#### Intervention (MATCH-ADTC)

MATCH-ADTC consists of a manual, a training package, and a monitoring and feedback system (the eMonitor in this study). Clinicians participated in an initial five day training of block teaching, as well as weekly small group telephone or Skype consultation sessions, led by an accredited MATCH-ADTC expert to support ongoing fidelity to the model. MATCH-ADTC comprises 33 modules or specific treatment procedures. Clinicians delivering MATCH-ADTC follow structured and specific treatment procedures, as outlined in the MATCH-ADTC manual. At the start of treatment, a clinician meets with the youth participant and the youth’s family and they collaboratively establish top problems to be addressed in therapy, thus providing the participant and their family an integral role in defining the goals for therapy. Following this, clinicians (with the support of a MATCH-ADTC expert) are guided by an evidence-based algorithm to ensure that treatment is best tailored to the youth’s clinical presentation. Each MATCH-ADTC module contains details about the therapy session, including such resources as therapy worksheets, homework assignments, and caregiver handouts. Clinicians use a web-based system (the eMonitor, designed purposefully for this trial), which provides a weekly summary of the participant’s progress (based on the results of the Brief Problem Monitor and Top Problem Assessment), to monitor their client’s progress and adapt therapy in consultation with the youth and the youth’s family.

#### Intervention fidelity

MATCH-ADTC therapists have weekly phone or Skype supervision where treatment for each youth is reviewed. Clinicians follow the MATCH-ADTC manual with the support of a MATCH-ADTC expert. All sessions (MATCH-ADTC and usual care) are audio-recorded and a randomly selected subset will be coded for evidence-based therapy content.

#### Control (usual care)

Usual care is the treatment that is usually provided to a youth at a CAMHS (e.g., case management, individual therapy, family therapy, medication, psycho-education, or a combination of these). Information on the usual care provided to each participant is collected. Clinicians providing usual care do not have access to the weekly progress data on the eMonitor, as this is not part of usual care.

Clinicians providing both MATCH-ADTC and usual care receive support from their team leaders and clinical managers, but MATCH-ADTC clinicians are instructed not to discuss with the rest of their team the treatment approaches they are using with their MATCH-ADTC clients, to ensure there is no contamination. This approach was used successfully in the study in the USA [30].

### Outcomes and measures

#### Primary outcomes

The three primary outcomes each address one of the three central aims of the trial: (i) the difference in trajectory of change of clinical severity between groups, using the parent-rated Brief Problem Monitor [42]; (ii) clinicians’ use of evidence-based content during therapy sessions (based on audio-recorded therapy sessions); (iii) total time spent by clinicians delivering therapy (using therapy logs).

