### Sample size

Overall, a sample size of 60 clinicians and 400 patients will provide sufficient power to detect effect sizes of approximately 0.37, well below the effect size shown by the comparable USA study [30]. The initial power calculation was to allow independent analysis to be undertaken for Māori and Pacific participants and ensured sufficient power (80 %) to detect moderate effect sizes of between 0.61 and 0.70 as statistically significant (two-tailed *α* = 0.05) in these groups (equivalent to the effect sizes found in the USA study [30]). This estimate allowed for a 15 % attrition rate in clinicians and in clients (based on the 12.3 % attrition rate reported in Weisz *et al.* [30] and adjustment for the clustering of patients with clinicians (intraclass coefficient = 0.1)). We assumed approximately six to eight patients per clinician (approximately 400 patients). If fewer clinicians were available within the targeted services, we planned to increase the number of participants per clinician to ensure that we maintained statistical power. The intention was to recruit approximately 12 clinicians working in Kaupapa Māori services and approximately 12 clinicians working in Pacific services. While this seemed feasible in the planning stages, when we were actually conducting the trial, there were a number of staffing difficulties in the services overall, and these impacted more particularly in the Kaupapa Māori and Pacific services, perhaps because of the smaller pool of people in the workforce. This led to difficulty in recruiting clinicians working in Māori and Pacific services, with resulting reduced ability to recruit participants to the trial from those services. It became evident that we would not reach the targets for Māori and Pacific participants to allow ethnic-specific analysis, as planned. An interim blinded-to-treatment allocation, single group, power analysis was undertaken (when approximately 50 participants had completed treatment) to determine the total number of participants needed to show overall clinical effectiveness for the whole sample. This summary produced a standard deviation for the change in the parent-rated Brief Problem Monitor of 4.4, which indicated that to show a clinically important difference in the change (>2 units) as statistically significant (two-tailed *α* = 0.05) with 80 % power, a total sample size of 160 participants would need to be recruited. A total sample of 200 participants would provide 90 % power for this comparison. Although a reduced final sample size would compromise the ethnic-specific analysis, it was felt that the primary question of whether MATCH-ADTC improved the trajectory of change of clinical severity more than usual care could be conclusively addressed with 200 participants. Based on the ongoing recruitment, it was anticipated that this total recruitment could be achieved if we extended the timeline and recruited until the end of June 2015.

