#### Overall analysis

The comparability of the baseline status of both treatment groups (i.e., MATCH-ADTC and usual care) will be determined using descriptive analysis, in terms of age, sex, clinical symptom severity, diagnosis, and ethnicity. The two randomized treatments may vary in duration, so that post-intervention and follow-up (three months after treatment has ended) analyses are potentially confounded by treatment duration. To allow an unconfounded interpretation, we propose to use the trajectories of change across time on the parent-rated Brief Problem Monitor as our primary outcome measure. The trajectory of change was selected in part because the duration of treatment and number of sessions provided to individual youth are variable in usual clinical services, and also within the structure of the MATCH-ADTC program, such that the usual care and MATCH-ADTC groups could not be matched for duration or number of sessions. In addition, we want to compare the results of the current study with that of a trial from the USA that used this method [30]. The primary analysis will be based on the intention-to-treat population, but sensitivity analysis will be undertaken on the per-protocol population.

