##### Delivery of evidence-based treatments

The percentage of evidence-based content and quality of delivery of therapy in a 10 % random subset of sessions assessed by coding audio-taped therapy sessions will be compared between groups using an analysis of variance (ANOVA) model, following the method used in the trial in the USA study [30].

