##### Efficiency of service delivery

Efficiency in delivery of therapy for MATCH-ADTC and usual care will be compared using ANOVA to test for significant differences using the following data which will be collected from the clinical service, including:Clinician time (in minutes);Duration of contact with the service (in weeks);Number of therapy sessions; andNumber of missed therapy sessions.

If any of these outcomes do not meet the assumptions for parametric ANOVA models, the data will be transformed as appropriate prior to analysis.

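### The article does not fix which measures are primary: aim (iii) rests on one, two or four measures depending on the section, and aim (ii) on one or two

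*Protocol article*

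**What the plan says.** The protocol article describes the primary measures in several places.

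- **Abstract (Methods), and Outcomes and measures, Primary outcomes.** Three outcomes, one per aim: "The three primary outcomes each address one of the three central aims of the trial". They are the parent-rated Brief Problem Monitor trajectory, evidence-based content of recorded sessions, and total clinician time from the therapy logs.
- **Primary hypotheses.** Hypothesis (iii) is measured by two variables, clinician minutes and weeks of contact with the service. It is worded as efficiency at least as good as usual care, not strictly better.
- **Statistical methods, Overall analysis.** "we propose to use the trajectories of change across time on the parent-rated Brief Problem Monitor as our primary outcome measure".
- **Sample size.** The revised target is justified on one question only: "it was felt that the primary question of whether MATCH-ADTC improved the trajectory of change of clinical severity more than usual care". The calculation uses "a standard deviation for the change in the parent-rated Brief Problem Monitor of 4.4" and seeks to show the difference "as statistically significant (two-tailed *α* = 0.05) with 80 % power".
- **Statistical methods, Primary outcomes, Delivery of evidence-based treatments.** Two quantities are compared by ANOVA: "The percentage of evidence-based content and quality of delivery of therapy".
- **Statistical methods, Primary outcomes, Efficiency of service delivery.** Four measures are to be tested for significant differences: clinician minutes, "Duration of contact with the service (in weeks"), number of sessions and number of missed sessions.
- **Secondary outcomes.** Quality of delivery, weeks of contact, number of sessions and missed sessions are not listed.

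**The concern.** A reader cannot tell from the article whether the efficiency aim stands or falls on one, two or four measures, or whether the content aim rests on percentage alone or on percentage and quality. The extra measures are not secondary by default, because the secondary list omits them. Quality, number of sessions and missed sessions get their only status from sitting under an analysis heading that says primary. Weeks of contact has that and also stands in a primary hypothesis.

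The efficiency measures can disagree. One arm might have fewer sessions but more minutes, or fewer minutes spread over more weeks. With no deciding measure named, the choice could be made after the results are known. The Discussion ties positive results to making MATCH-ADTC part of core training for clinicians, so the choice has consequences.

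**Working it through.** **1. The plan's own figure.** Inputs from Sample size: difference 2 units, SD 4.4, two-sided alpha 0.05. Allocation is 1:1 (Design).

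Power ≈ Φ( δ / (SD·√(2/n)) − 1.96 ), with n per arm.

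- n = 80: 2 / (4.4·√(2/80)) = 2.875; Φ(0.915) = 82.0%, against 80% stated.
- n = 100: 2 / (4.4·√(2/100)) = 3.214; Φ(1.254) = 89.5%, against 90% stated.

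The stated figures are reproduced to within 2 points. They use the full 0.05 on the Brief Problem Monitor. No other primary outcome enters the revised calculation.

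**2. Measures per aim, by section.**

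| Section | Aim (i) clinical | Aim (ii) content | Aim (iii) efficiency |
|---|---|---|---|
| Abstract; Outcomes and measures | 1 | 1 | 1 (total time) |
| Primary hypotheses | 1 | 1 | 2 (minutes, weeks) |
| Statistical methods, under Primary outcomes | 1 | 2, if quality is tested separately | 4 |
| Overall analysis | 1, called the primary measure | not mentioned | not mentioned |

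Aim (i) is the same measure throughout. The count for aim (ii) changes once and for aim (iii) twice.

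**3. What several tests inside one aim could cost.** Suppose each aim is a separate claim with its own 5%, every test is run at two-sided 0.05, there is no true difference on any measure in the aim, and any one significant result is taken to support the aim. For k independent tests the false-positive chance is 1 − 0.95^k.

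- Aim (iii), k = 4: 1 − 0.95⁴ = 18.5%.
- Aim (ii), k = 2: 1 − 0.95² = 9.8%.

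**4. Sensitivity to correlation.** The article gives no correlations, so these are assumptions: multivariate normal test statistics with one common correlation.

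| Assumed correlation | k = 4 | k = 2 |
|---|---|---|
| 0 | 18.5% | 9.8% |
| 0.5 | 15.6% | 9.1% |
| 0.7 | 13.0% | 8.4% |
| 0.9 | 9.4% | 7.0% |

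The four efficiency measures describe the same therapy contacts, so correlation is likely and 18.5% is an upper figure.

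**5. Sensitivity to direction.** Counting only errors in favour of MATCH-ADTC, independent tests give 1 − 0.975⁴ = 9.6% and 1 − 0.975² = 4.9%, against 2.5% for a single test.

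**The case against.** **The design is three aims with three outcomes, and the rest is loose wording.** On this view, Overall analysis only explains why clinical change is analysed as a trajectory when treatment duration varies, and sizing a trial on one of several primary outcomes is ordinary. Much of this stands. A reader might infer that the article adopts a single primary outcome and demotes the other two. It does not: the Abstract, the hypotheses and the outcomes section all keep three. The wording in Overall analysis still needs correcting, but it is the lesser part of the problem.

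**The testing order and alpha split may be in an analysis plan that is not shown.** This stands, and their absence is not part of the point. An unseen plan would not remove the disagreement between sections of the published text.

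**A larger error rate is tempting but unsupported.** Counting three to seven primary tests gives 1 − 0.95³ = 14.3% to 1 − 0.95⁷ = 30.2%, and a reader might take that as the trial's false-positive rate. It would require that any one significant result makes the whole trial positive, a rule the article never adopts; the outcomes section ties each outcome to its own aim. It would also require independent tests, no true difference on any of the measures, and 0.05 for every test, whereas alpha is stated only in the power calculations.

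**Hypothesis (iii) is not a superiority claim.** Correct. A difference-test error rate maps imperfectly onto a claim of efficiency at least as good as usual care, so 18.5% is only a guide. It is also unclear whether quality is a separate test, so the 9.8% is conditional.

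Treating the aims as separate claims does not settle matters inside aims (ii) and (iii), where several measures still compete and none is named as deciding.

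**Conclusion.** The point holds as an inconsistency about which measures are primary, chiefly for aim (iii) and to a lesser degree for aim (ii). It should be corrected.

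The possible size is a false-positive chance of up to 18.5% for the efficiency aim and up to 9.8% for the content aim, in place of 5% each. This rests on four assumptions: any one result counts, tests are independent, each is run at two-sided 0.05, and there is no true difference on the measures in that aim. At assumed correlations of 0.5 to 0.9 the figures fall to 15.6–9.4% and 9.1–7.0%. The contradiction between sections does not depend on any of these figures.

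The clinical outcome is unaffected: its measure is the same throughout, and its stated power is reproduced.

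**What to change.** Align the other sections with Primary outcomes under Outcomes and measures:

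1. Name one primary measure per aim: parent-rated Brief Problem Monitor trajectory, percentage of evidence-based content, total clinician minutes. Use the same three in Primary hypotheses and in the analysis section headed Primary outcomes.
2. Add quality of delivery, weeks of contact, number of sessions and number of missed sessions to Secondary outcomes, and analyse them there.
3. In Overall analysis, call the trajectory the primary clinical outcome.
4. State that each primary result supports only its own aim.

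The change is wording only, and Trial status says recruitment is still open. The downside is that the four moved measures can then only be supportive.

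A fixed testing order starting with the Brief Problem Monitor is optional and not part of this fix. It would leave that outcome's power intact, but content and time could not be confirmatory if the clinical result failed, although the article presents the three aims without ranking them.

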#### Secondary outcomes

Other clinical outcomes are measured using: the youth-rated Brief Problem Monitor [42], the parent- and youth-rated Strengths and Difficulties Questionnaire [43], the parent- and youth-rated Top Problems Assessment [44], the youth-rated Child Health Utility [45], the number and type of diagnoses using the Development and Well-Being Assessment [46, 47], prescribed medications (and dosage) for psychiatric conditions.

Further secondary outcomes include:Clinician self-report of the treatment provided based on the Therapy Procedures Checklist [48];Clinician’s satisfaction with therapy based on the Therapist Satisfaction Inventory [49];Client satisfaction with therapy based on a treatment satisfaction questionnaire;The number and types of serious adverse events and moderate adverse events.

### Outcome measures

The following outcome measures are collected during the trial. Most clinical measures are collected during the weekly telephone calls made by the research assistants according to the schedule of assessments listed in Table 1.

**Table 1 Tab1:** Summary schedule of data collected

Measure	Baseline	During therapy	After intervention	3-month follow-up	Informant	Collected by
Demographics	×				Child and parent	Clinician
Strengths and Difficulties Questionnaire	×	monthly	×	×	Child and parent	Research assistant
Brief Problem Monitor	×	weekly	×	×	Child and parent	Research assistant
Top Problems Assessment	×	weekly	×	×	Child and parent	Clinician at baseline and research assistant weekly
Development and Well-Being Assessment	×		×		Child (if 11 or over) and parent	Research assistant supports the family to complete online
Child Health Utility	×		×	×	Child	Research assistant
Medication use	×		×	×	Clinician and parent	Clinician at baseline and after intervention, research assistant at 3 months
Client satisfaction			×		Child and parent	Research assistant
Therapy Procedures Checklist			×		Clinician	Clinician
Serious adverse events		×			Clinician	Clinician
Moderate adverse events				×	Parent	Research assistant
Therapist Satisfaction Inventory			×		Clinician	Clinician
Recordings of therapy sessions		×			Clinician	Clinician
Therapy log			×		Clinician	Clinician

The Brief Problem Monitor [42] is a 19-item assessment using data from parents and youth to measure internalizing, externalizing, hyperactivity, and total problems. It is based on the widely used Child Behavior Checklist [50] and Youth Self-Report [51], both of which have sound psychometric qualities. The Brief Problem Monitor can be administered by phone, taking approximately five minutes to complete per administration, making it a practical and robust measure of the trajectory of change in clinical symptoms over time.The Top Problems Assessment has been developed to allow the youth and family to identify and rate the severity of the three top problems that they would like addressed in therapy. There is good evidence for reliability, validity, and sensitivity to change for this assessment [44].The Strengths and Difficulties Questionnaire [43] is a scale used widely in both research and practice. It produces a total score with five subscales: emotional symptoms, conduct problems, hyperactivity, peer relationship problems, and prosocial behavior. It has a satisfactory internal consistency, test–retest reliability, and inter-rater agreement [52].Child Health Utility [45] is a nine-item measure of health-related quality of life designed specifically for children. Each item taps into a different domain (i.e., worry, sadness, pain, tiredness, annoyance, school, sleep, daily routine, and activities) in reference to how a child feels ‘today’. This is a preference-based instrument that generates utility weights and which allows for the calculation of quality-adjusted life years for use in health economic evaluations. The internal consistency has been reported sound and the convergent validity against the Strengths and Difficulties Questionnaire is in the moderate-to-strong range [53].The Development and Well-Being Assessment [46] is an online diagnostic tool. It is designed to indicate likely psychiatric diagnoses in 5–16-year-olds based on in-built diagnostic algorithms. This assessment has been validated in both community and clinic samples in the UK [46]. Inter-rater agreements between the Development and Well-Being Assessment and clinician diagnoses are moderate to high [54–56].Client satisfaction questionnaires. The parent-rated measure has nine questions (eight-rated on a Likert scale and one open-ended item). The youth-rated satisfaction questionnaire includes seven questions (four rated on a Likert scale and three open-ended items). Likert-rated questions ask the informant to provide feedback on the quality of treatment, whether it helped, and if they would recommend it to others. The open-ended questions were designed to elicit what the participants liked most or least about the treatment and how treatment could be improved.The Therapist Satisfaction Inventory is a 16-item questionnaire (adapted from [49]), which assesses how satisfied a clinician feels about the intervention provided.The Therapy Procedures Checklist is a treatment description questionnaire, which consists of 62 items describing common psychotherapeutic processes (i.e., psychodynamic, cognitive, and behavioral techniques) that may have been used in the course of therapy. Each item is rated on a five-point Likert scale from ‘rarely’ to ‘most of the time’. The instrument is adapted from an earlier version of the Therapy Procedures Checklist, which has been shown to have good content validity, internal consistency, and test–retest reliability [48].The medication use questionnaire collects data on prescribed medications (and dosage) for psychiatric conditions.

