#### Weekly measurements

The allocated research assistant completes the weekly telephone assessments with the parent and the youth participant for the duration of treatment. The weekly assessment is designed not to exceed 10 minutes, to minimize participant burden.

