#### Post-intervention assessment

The post-intervention assessment occurs once a clinician has discharged the youth from treatment and is conducted by the research assistant.

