#### Three month follow-up

Three months after the post-intervention assessment, a final follow-up assessment is conducted by the research assistant.

Participant flow is outlined in Fig. 1. The study procedures are summarized in Table 1.

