### Blinding

Owing to the nature of the study, double blinding is not possible, as clinicians are aware of the treatment they are administering. We anticipate that despite signing informed consent, most youth and their parents will effectively be blind to treatment allocation. At entry to the study, the information conveyed to the participants (orally and in writing) has been designed to ensure that details that could easily distinguish MATCH-ADTC from usual care are not provided, but that accurate information is given. We explain that both treatments are thought to be effective and that the purpose of this research is to compare treatments to see if one is better than the other. All research assistants collecting telephone administered assessments and coding the therapy sessions are blind to treatment allocation throughout the study. Participants are asked not reveal the details of the intervention they are receiving to the research assistant. All participants are given an identification number to ensure that the researchers involved in data management and manipulation are unaware of the treatment allocation.

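### Research assistants who must stay blind are also assigned to collect families' open-ended comments on the treatment, before the 3-month outcomes are taken

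*Protocol article*

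**What the plan says.** The Outcome measures section describes two client satisfaction questionnaires. One of the nine parent items and three of the seven youth items are open-ended. Their purpose is stated: "The open-ended questions were designed to elicit what the participants liked most or least about the treatment and how treatment could be improved". Table 1 schedules the questionnaire once, after the intervention, with child and parent as informants and the research assistant as collector.

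The same role carries the outcome assessments. Under Weekly measurements: "The allocated research assistant completes the weekly telephone assessments with the parent and the youth participant for the duration of treatment". Under Post-intervention assessment: "The post-intervention assessment occurs once a clinician has discharged the youth from treatment and is conducted by the research assistant". Under Three month follow-up: "Three months after the post-intervention assessment, a final follow-up assessment is conducted by the research assistant".

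The Blinding section says that research assistants who take telephone assessments or code sessions remain blind for the whole study. It gives one safeguard on the family's side: "Participants are asked not reveal the details of the intervention they are receiving to the research assistant". It also expects most families to be unaware, in effect, of which treatment they are getting. The abstract describes the trial as assessor-blinded.

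**The concern.** One instruction asks families to keep details of their treatment from the research assistant. Another has the research assistant collect free comments on that treatment. An informative answer to the open items tends to include the kind of detail that the safeguard is meant to keep back.

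The timing makes this matter. The questionnaire falls after the intervention, and research assistants still have a full round of outcome ratings to collect three months later. An assessor who has learned or guessed the arm may probe, prompt or record differently. Clinicians are not blind, so the assessor blind is the trial's main protection against biased collection of these ratings.

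**Working it through.** The article gives no figure to reproduce on this point, so the check sets its statements side by side.

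1. **Who collects the comments, and when.** Table 1: the research assistant, after the intervention, from child and parent. The article fixes this itself and does not leave it to another document.

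2. **What is collected.** One open parent item and three open youth items about the treatment. They do not ask for the arm or for named procedures.

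3. **What the blind requires.** The Blinding section keeps the assessors blind for the whole study, so the requirement does not lapse at discharge. The request to families concerns details of the intervention, which is broader than the name of the arm. A family that does not know its arm can still describe it.

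4. **Whether such details could identify the arm.** Some could. Under Intervention, MATCH-ADTC clinicians use a weekly progress summary from the eMonitor to adapt therapy together with the youth and family. Under Control, usual-care clinicians have no access to those weekly data. A comment that the clinician went over the weekly scores would point to MATCH-ADTC. Worksheets or homework are weaker clues: usual care can include individual therapy, and clinicians in both arms may already have cognitive behavioral or parent training, since that was a stratification factor.

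5. **Which ratings are exposed.**
   - *Weekly ratings during therapy:* collected before the questionnaire, so not exposed through this route.
   - *Post-intervention ratings by the research assistant* (Brief Problem Monitor, Strengths and Difficulties Questionnaire, Child Health Utility): exposed only if satisfaction is asked first. The order is not stated.
   - *3-month ratings* (the same three instruments, the Top Problems Assessment, medication use and moderate adverse events): all collected after the questionnaire. They are exposed if the follow-up assessor received, or has seen, the answers.

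6. **Whether anything reconciles the statements.** The article mentions no separate collector, no private completion and no item order that would protect the blind.

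7. **Reach into the primary outcome.** The primary clinical outcome is the trajectory of the parent-rated Brief Problem Monitor. Most of its points are the weekly ratings. At most the post-intervention point is affected, and the 3-month point if it enters the model, which the article does not say.

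**The case against.** The strongest reply is that this is a possible leak and not a demonstrated breach. A reader might infer that the assistant has to put these questions to families in a telephone call, that the two instructions cannot both be followed, and that the blind is therefore broken for every family. The article does not support this. Table 1 says only who collects the form. The Post-intervention assessment section gives no mode of contact, and a self-completed form handed to the assistant would fit the text. Item order is not stated. An allocated assistant is mentioned only for the weekly calls, so the same person at three months is plausible but not established. A family can also answer about the clinician, the timing or how helpful the sessions were, and disclose nothing about the arm. Families were deliberately not given distinguishing details at entry. All of this stands.

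It is also fair to say that a condensed article leaves mode and order to the full protocol. That removes any criticism for not stating them. It does not remove the point, because the collector, the timing, the content of the items and the blinding rule are all stated in the article, and together they create the risk.

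Finally, the request to families is worded for the intervention that they are receiving, which could be read as ending at discharge. The assessors' own blind is stated for the whole study, so that reading does not resolve the conflict.

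**Conclusion.** The point holds as an unreconciled conflict between Table 1, read with the description of the satisfaction questionnaires, and the Blinding section. It puts the assessor blind at risk chiefly for the 3-month ratings, and for the post-intervention ratings if satisfaction is asked before them. It does not touch the weekly ratings during therapy, and unblinding is not certain.

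The size cannot be given as a number. A reader might be tempted to assume a shift of 0.1 to 0.2 SD, multiply by the stated SD of 4.4 (0.1 × 4.4 = 0.44; 0.2 × 4.4 = 0.88 units), and compare the result with the 2-unit difference (0.44 / 2 = 22 %; 0.88 / 2 = 44 %). That does not describe bias in this trial. The shift is not in the article, and 4.4 is the SD of change in the pooled interim sample. The comparison would also need every family's assessor to be unblinded and the shift to differ between arms by the full amount. And it treats an error in one or two late ratings as if it moved the whole trajectory.

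The conclusion assumes that some families would mention arm-specific features, and that the follow-up assessor has received or seen their answers. Both are plausible and neither is established. It is a cheap improvement worth making, and it does not count against the primary analysis as a whole.

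**What to change.** Change the client satisfaction line in Table 1 in one of two ways, and add a sentence to the Blinding section to match.

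- **Private self-completion.** Parent and youth fill in the form on paper or online and submit it without the outcome assessor seeing the answers. The post-intervention Development and Well-Being Assessment session should not be used for this unless submission is private: a research assistant supports that session, and children under 11 are not informants in it, whereas satisfaction is collected from child and parent across the trial's age range of 7 to 14.
- **Last item at three months.** Ask satisfaction at the end of the 3-month contact, once every outcome rating has been recorded.

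The first option may lower the return slightly and needs one form. The second adds three months of recall. Either one changes the mode or timing of a secondary outcome partway through: recruitment is under way, and about 50 participants had already completed treatment at the interim check. Record the date of the change, and report satisfaction collected before and after it separately or with that difference noted. For families already assessed, the report should state who collected the satisfaction answers, in what mode and order, and whether the same person took the 3-month ratings.
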